### Pancreatic Enzyme Abnormalities and/or Pancreatitis

Any subject with pancreas enzyme (amylase and/or lipase) elevations, and/or clinical evidence of pancreatitis, should be promptly evaluated by the treating investigator. Treatment-emergent elevations in excess of  $2 - 3 \times \text{ULN}$  should trigger urgent evaluation, particularly when accompanied by other clinical signs and/or symptoms of pancreatitis.

The following are guidelines for dose reduction, delay, and discontinuation of ABBV-467 in the setting of pancreatic abnormalities:

- **Elevations in amylase/lipase:** If isolated elevation of enzymes without signs or symptoms of pancreatitis, perform evaluation of pancreatitis by clinical assessment, abdominal computed tomography with contrast, and/or MRCP, consider other causes for elevated amylase/lipase. Additional grade-specific recommendations include:
  - Grade 3 increase in amylase and/or lipase ( $>2.0 - 5.0 \times \text{ULN}$  with signs or symptoms of pancreatitis;  $> 5.0 \times \text{ULN}$  regardless of signs/symptoms): ABBV-467 should be immediately interrupted, and the sponsor notified. At joint discretion of the investigator and sponsor, the subject may resume treatment, but only after the toxicity resolves to Grade 1 or lower, or to baseline if the toxicity was  $> \text{Grade 1}$  at the time of study entry. In such instances, ABBV-467 should be resumed at a dose that is at least 33% lower than the previous dose.
  - Grade 4 increase in amylase and/or lipase ( $> 5.0 \times \text{ULN}$  with signs and/or symptoms of pancreatitis): ABBV-467 should be immediately and permanently discontinued, and the sponsor notified.
- **Pancreatitis:** For any instance of pancreatitis (regardless of grade), ABBV-467 should be immediately held, and the sponsor notified:
  - Grade 2 (enzyme and/or radiographic findings in absence of either clear signs/symptoms of pancreatitis or need for intervention): At joint discretion of the investigator and sponsor, the subject may resume treatment, but only after the toxicity resolves to Grade 1 or lower. In such instances, ABBV-467 should be resumed at a dose that is at least 33% lower than the previous dose.

- Grade 3 - 4 (signs and/or symptoms of pancreatitis with medical intervention required): ABBV-467 should be immediately and permanently discontinued, and the sponsor notified.

Pancreatitis will be graded based on the criteria in the table below, adapted from CTCAE v5.0.

| MedDRA SOC                 | CTCAE Term   | Grade 1 | Grade 2                                    | Grade 3                                                                                      | Grade 4                                                      |
|----------------------------|--------------|---------|--------------------------------------------|----------------------------------------------------------------------------------------------|--------------------------------------------------------------|
| Gastrointestinal disorders | Pancreatitis | -       | Enzyme elevation; radiologic findings only | Severe pain; vomiting; medical intervention indicated (e.g., analgesia, nutritional support) | Life-threatening consequences; urgent intervention indicated |

CTCAE = Common Terminology Criteria for Adverse Events; MedDRA = Medical Dictionary for Regulatory Activities; SOC = system organ class

In addition to the above, all local standards of care should be followed with respect to diagnostic and therapeutic interventions, including bowel rest, imaging, endoscopy, and/or gastroenterology consult.

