| 4-week (5-dose) IV infusion with a 4-week recovery period in Sprague-Dawley rat (CrI:CD®(SD))
aged 10 weeks at initiation of dosing | 
 
• 10/sex (main)
 
• 5/sex for recovery (control, mid, high)
 
 | 0, 10, 30, 60, 100  | Effects observed in 
 
• Pancreas – single-cell necrosis, increased amylase and lipase
 
• Liver – increased ALT/AST, multinucleated hepatocytes
 
• Bone marrow – decreased cellularity, red and white blood
 
• Gastrointestinal tract – epithelial degeneration and regeneration
 
• Lymphoid system – lymphoid cell depletion and/or necrosis in multiple lymphoid tissues
 
• Testes – degeneration/atrophy of seminiferous tubules
 
• Multiple other tissues – single-cell necrosis
 
                                                                                                                                                                                                          |
| 4-week (5-dose) IV infusion with a 4-week recovery period in beagle dog
aged 8-8.5 months at initiation of dosing                   | 
 
• 4/sex (main)
 
• 2/sex for recovery (control, mid, high)
 
  | 0, 1, 3, 10         | Mortality at 10 mg/kg after 1 or 2 doses (days 3–10) attributed to on-target effects in gastrointestinal tract, pancreas, and bone marrow
Effects observed in 
 
• Pancreas – single-cell necrosis, acinar atrophy/necrosis, and increased amylase and lipase
 
• Liver – profound increases in ALT and AST, hepatocyte necrosis, bile cholestasis
 
• Bone marrow – decreased cellularity, red and white blood
 
• Gastrointestinal tract – necrosis and/or hemorrhage
 
• Lymphoid system – decreased circulating lymphocytes, lymphoid cell necrosis in multiple lymphoid tissues
 
• Testes – degeneration/atrophy of seminiferous tubules
 
• Multiple other tissues – single-cell necrosis
 
 |

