### ABBV-467 Dosing Modifications for Toxicity

After Cycle 1, doses of ABBV-467 can be delayed up to 1 day due to toxicity; delays any longer than 1 day should result in the dose being skipped. If the Day 8 dose is skipped or delayed, the subject should resume dosing on Day 15 (provided that any toxicities requiring dose delay or interruption have resolved), and so on. If the Day 22 dose is skipped or delayed, the subject should complete the 28-day cycle on schedule and resume dosing at the start of the next cycle (provided that any toxicities requiring dose delay or interruption have resolved). If the ABBV-467 Day 1 dose of any cycle is delayed, then the start of the cycle should be delayed until the next dose of ABBV-467 is administered.

For any subject who experiences Grade 3/4 toxicity which is attributed to ABBV-467, the dose will be held until the toxicity resolves to Grade 1 or lower, or to baseline if the toxicity was > Grade 1 at the time of study entry. Upon toxicity resolution, the subject may restart study drug at 75% of that subject's starting dose (i.e., a 25% dose reduction). Following similar guidelines, subsequent dose reductions to 50% of the starting dose, and then a 25% of the starting dose, may be implemented. Dose reductions below 25% of the subject's starting dose are not allowed.

In addition, subjects with AML who experience CR or PR with hematologic recovery after receiving ABBV-467 and then experience Grade > 3 hematologic AE should undergo a bone marrow evaluation to determine if cytopenias are due to drug toxicity or recurrent disease.

Study drug interruptions for events that are considered not related to the study drug (e.g., underlying cancer, planned surgical procedures or acute viral illnesses), should not necessitate a dose reduction. The timing of dose resumption should be at the discretion of the Investigator.

Subjects experiencing a delay longer than 28 days due to an AE(s) related to study treatment should be permanently discontinued from study treatment. Subjects experiencing a delay longer than 28 days unrelated to study treatment must be discussed with the AbbVie TA MD or designee.

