## 6.3 Dose-Limiting Toxicity

---

Dose-limiting toxicity for dose escalation purposes will be determined on events that occur during the first 28-day cycle.

Any AE of Grade 3 or higher will be considered a DLT, unless toxicity can solely be attributed to the underlying disease, with the following clarifications. Adverse events of any grade resulting in discontinuation of study drug will be considered a DLT. Missing any dose as a result of toxicity unexplained by the underlying disease will also be considered a DLT.

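### The Grade 3 amylase/lipase rule contains every Grade 4 case, so Section 6.2 both allows and forbids later re-exposure of a symptomatic subject above 5 × ULN

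*Protocol*

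**What the plan says.** Section 6.2, under Pancreatic Enzyme Abnormalities and/or Pancreatitis, ties the dosing action to the grade of the amylase or lipase increase.

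- **Grade 3 enzyme rule.** It covers more than 2.0 and up to 5.0 × ULN with signs or symptoms of pancreatitis. It also covers more than 5.0 × ULN "regardless of signs/symptoms): ABBV-467 should be immediately interrupted, and the sponsor notified". If investigator and sponsor agree, "the subject may resume treatment, but only after the toxicity resolves to Grade 1 or lower, or to baseline if the toxicity was" above Grade 1 at study entry. The resumed dose must be at least 33% below the previous one.
- **Grade 4 enzyme rule.** It covers more than 5.0 × ULN "with signs and/or symptoms of pancreatitis): ABBV-467 should be immediately and permanently discontinued, and the sponsor notified".
- **Pancreatitis rule, Grade 3–4.** It covers "signs and/or symptoms of pancreatitis with medical intervention required): ABBV-467 should be immediately and permanently discontinued".

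The grading table that follows has a row for pancreatitis only. Its Grade 3 entry names severe pain, vomiting and "medical intervention indicated (e.g., analgesia, nutritional support"). It has no row for amylase or lipase.

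**The concern.** The second limb of the Grade 3 enzyme rule applies whether or not the subject has symptoms. It therefore takes in the symptomatic subjects whom the next bullet defines as Grade 4. For them, one bullet keeps later treatment open and the other closes it for good, and no order of precedence is given.

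The pancreas is a documented target organ. In the 4-week dog study (Supplementary Table S7), deaths at 10 mg/kg after one or two doses were "attributed to on-target effects in gastrointestinal tract, pancreas, and bone marrow", and the same study reports raised amylase and lipase. Section 4.2 names the dog as the species for setting the human starting dose. Up to 25 sites will apply the rule. Whether a symptomatic subject may be treated again should not depend on which bullet the reader stops at.

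**Working it through.** The plan gives no figure to reproduce. The check is whether the two definitions overlap, and then what each allows in the overlap.

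**1. The definitions.** Let x be the enzyme level in multiples of ULN and S mean that signs or symptoms of pancreatitis are present.

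- Grade 3 = {2 < x ≤ 5 and S} or {x > 5, with or without S}
- Grade 4 = {x > 5 and S}

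| Enzyme level | Symptoms | Meets Grade 3 | Meets Grade 4 | Later treatment |
|---|---|---|---|---|
| 2 < x ≤ 5 | yes | yes | no | may be considered |
| x > 5 | no | yes | no | may be considered |
| x > 5 | yes | yes | yes | may be considered **and** forbidden |

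Grade 4 is a complete subset of Grade 3. The conflict is confined to the last row, but it covers all of Grade 4.

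**2. Text that might settle it.**

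- The general rule in Section 6.2 says: "For any subject who experiences Grade 3/4 toxicity which is attributed to ABBV-467, the dose will be held until the toxicity resolves". It then allows a restart at 75% of the starting dose. It gives no precedence to organ-specific rules and does not itself enforce a permanent stop.
- Section 6.1 has investigators grade adverse events by CTCAE v5.0 and forbids overlapping dates when severity rises. That governs recording. It does not say that the higher grade decides dosing.
- Operations Manual Section 4.2 uses the most severe grade, but for tabulating adverse events.
- The Grade 3–4 pancreatitis bullet stops treatment permanently where medical intervention is required. A symptomatic subject above 5 × ULN who needs none is not caught by it.

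None of these resolves the last row. By contrast, the hepatic rules in Section 6.2 and Appendix H use separate bands: from 3 to below 5 × ULN with one restart condition, and 5 × ULN or more with another.

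**3. Size of the difference.** Under the Grade 3 rule the highest resumed dose is 100% − 33% = 67% of the previous dose. Under the Grade 4 rule it is zero. Taking the previous dose as the full target dose in Table 2:

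| Dose level | Target (mg/kg) | Grade 3 maximum: target × 0.67 (mg/kg) | Grade 4 (mg/kg) |
|---|---|---|---|
| 1 | 0.16 | 0.107 | 0 |
| 2 | 0.32 | 0.214 | 0 |
| 3 | 0.53 | 0.355 | 0 |

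**4. Effect on dose escalation.** Section 6.3 states: "Any AE of Grade 3 or higher will be considered a DLT, unless toxicity can solely be attributed to the underlying disease". An event in Cycle 1 is thus a DLT by default at either grade, so DLT counts are essentially unaffected.

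**5. Check of the remedy.** If the second Grade 3 limb is limited to x > 5 without S, Grade 3 becomes {2 < x ≤ 5 and S} or {x > 5 and not S}. This shares no case with {x > 5 and S}, and each row of the first table then carries one instruction.

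**The case against.** The strongest reply is that the actions are keyed to grade and one event has one grade at a time. A symptomatic rise above 5 × ULN that is graded 4 follows the Grade 4 bullet. Only that reading gives the Grade 4 bullet any work to do, and most sites would apply the stricter and more specific line. This is plausible, but the protocol does not write it down for dosing, and the section's own definition places the same subject in Grade 3.

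Several limiting points stand:

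- Both rules require immediate interruption and sponsor notification, so there is no immediate hazard. A site that stops permanently complies with both.
- Resumption under the Grade 3 rule needs agreement of investigator and sponsor, resolution of the toxicity and a reduced dose. This is a real safeguard, although both parties would be reading the same conflicting text.
- Subjects who need medical intervention are already stopped under the pancreatitis bullet. The grading table also lists severe pain and vomiting at Grade 3, so the remaining group is probably mildly symptomatic.
- The dog deaths occurred at 10 mg/kg and involved three organ systems. They show why the pancreas is watched. They do not measure the risk of re-exposure at a reduced dose after recovery, and the dose figures above are permitted maxima, not risks.

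These points limit the seriousness. They do not remove the contradiction.

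**Conclusion.** The concern holds. As written, every Grade 4 amylase or lipase case also satisfies the Grade 3 rule, and the two rules disagree on whether later re-exposure may be considered. The difference is a dose of up to 67% of the previous one against none, or up to 0.355 mg/kg against zero at dose level 3, assuming the previous dose was the full target dose.

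The conflict bites mainly for subjects above 5 × ULN with signs or symptoms but no need for medical intervention. Their number cannot be estimated from the documents. Immediate management, adverse event grading and DLT counts are essentially unaffected. It should be corrected because it is a stopping rule for a known target organ, but it does not threaten the design or analysis.

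**What to change.** In the Grade 3 enzyme bullet of Section 6.2, change the limb above 5.0 × ULN so that it applies only *without signs or symptoms of pancreatitis*. Grade 3 is then more than 2.0 and up to 5.0 × ULN with symptoms, or more than 5.0 × ULN without them. Any symptomatic elevation above 5.0 × ULN leads to permanent discontinuation.

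The cost is one phrase and a short clarification to sites. Sample size, DLT criteria, adverse event grading and analysis need no change. The one thing given up is the option, by agreement of investigator and sponsor, to treat such a subject again.

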### Cardiovascular Toxicity

Due to MCL-1 expression on cardiac myocytes, there is a possibility that ABBV-467 may lead to cardiovascular toxicity including vital sign abnormalities (e.g., blood pressure, heart rate), chest pain, ECG abnormalities, and/or laboratory findings consistent with cardiac AEs.

Monitoring for cardiac toxicity will be performed as specified in the Protocol, [Appendix D](#), and the Operations Manual, and additional assessments may be performed as clinically indicated. If any such parameters (ECG, echocardiography, laboratory parameters, and/or clinical signs) suggest occurrence of cardiotoxicity, then a cardiology consult should be initiated and the TA MD should be informed and consulted. If the AE appears valid and there is no alternative cause, then ABBV-467 should be promptly interrupted, and the TA MD consulted prior to any resumption.

### Infusion Reactions and/or Allergic Reactions

Although the risk of infusion and/or allergic reactions with ABBV-467 is felt to be low, all subjects should be monitored for treatment-related AEs during all infusions, including measurement of vital signs every 30 minutes as specified in Operations Manual Section 3.11. For the initial 2 ABBV-467 infusions, subjects should remain at the site for monitoring for at least 2 hours following the completion of the 30 – 60-minute infusion (3 hours total). For subsequent infusions, post infusion monitoring is not required; however, vital signs should still be taken prior to start of infusion and every 30 minutes thereafter while the subject remains in the infusion area. Longer observation periods and more frequent vital sign evaluations are warranted in subjects who experience infusion reactions. ABBV-467 will be discontinued in the setting of Grade 4 infusion-related reactions.

If a Grade 2, Grade 3, or Grade 4 allergic reaction or infusion reaction is observed, ALL of the following measures are required:

- Immediate interruption of ABBV-467 treatment and discussion with the AbbVie TA MD before receiving any further treatment with ABBV-467.

- Appropriate medical therapy including epinephrine, corticosteroids, IV antihistamines, bronchodilators, and oxygen. Subjects should be carefully observed until the complete resolution of all signs and symptoms.
- Blood draw approximately 2 hours after the first sign of a reaction for the following laboratory tests: C3a, C5 complement functional assay, Immunoglobulin E level, and serum tryptase level.
- Collect unscheduled ABBV-467 PK samples.

## 6.3 Dose-Limiting Toxicity

---

Dose-limiting toxicity for dose escalation purposes will be determined on events that occur during the first 28-day cycle.

Any AE of Grade 3 or higher will be considered a DLT, unless toxicity can solely be attributed to the underlying disease, with the following clarifications. Adverse events of any grade resulting in discontinuation of study drug will be considered a DLT. Missing any dose as a result of toxicity unexplained by the underlying disease will also be considered a DLT.

### Non-hematologic DLTs (regardless of attribution)

- Grade 3 mucositis, nausea, vomiting, or diarrhea will only be considered a DLT if they require total parenteral nutrition, tube feeding, or prolonged hospitalization (> 72 hours).
- Any Grade 4 non-hematologic laboratory abnormality.
- Any instance of an AE that meets the definition of Hy's Law.

### Hematologic DLTs (regardless of attribution)

For subjects with MM, hematologic DLTs are defined as:

- Grade 4 neutropenia lasting for > 5 days.
- Grade 4 anemia unexplained by underlying disease.
- Febrile neutropenia defined as ANC < 1000/mm^3 with a fever ≥ 38.3°C or ≥ 38°C for 1 hour.
- Grade 4 thrombocytopenia.
- Grade 3 thrombocytopenia associated with clinically significant bleeding.

For subjects with AML, hematologic DLTs are as follows:

- ANC < 500/mm^3 and/or platelet < 25,000/mm^3 at either/both of the following time points (and only in the setting of a bone marrow response assessment showing < 5% blast count):
  - Day 42 from first dose of ABBV-467
  - 14 days beyond cessation of ABBV-467

For AML subjects with evidence of myelosuppression at 28 days, the DLT period will be 42 days or 14 days after bone marrow biopsy showing < 5% blast count (whichever is later). NOTE: In any instance in which bone marrow response assessment is either undocumented, or consistent with  $\geq$  5% blast count, cytopenias should be attributed to persistence of AML, rather than study drug (and therefore should not be considered DLT).

The DLT evaluation period will be 28 days irrespective of dose frequency (should other treatment schedules be explored).

Subjects who do not complete all of the scheduled doses of ABBV-467 or who do not receive at least 80% of the planned total dose during the DLT evaluation period, due to reasons other than occurrence of DLT(s) will be considered non-evaluable for DLT, and may be replaced to ensure the accrual of the minimum number of subjects to adequately assess tolerability (other subjects who withdraw consent or refuse further follow-up will be replaced). All safety information including information on AEs, etc., observed in subjects who are excluded from DLT evaluation will be taken into consideration to determine the next dose level.

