## Dose Escalation Guidelines

The goal of the dose escalation is to find the RP2D. The dose-escalation stage allows characterization of safety, tolerability, efficacy, PK, and PD data for each dose level while respecting the de-escalation and dose-elimination boundaries specified by the Bayesian optimal interval (BOIN) design. To maintain subject safety, all dose escalation parts will be guided by BOIN design based on the cumulative number of subjects who experience a dose-limiting toxicity (DLT) in a given ABBV-467 dose level. De-escalation and dose elimination will occur when instructed by the BOIN rules set forth in Table 1. However, if the BOIN rules recommend dose escalation or dose de-escalation, the escalation or de-escalation decision will be made in consideration of all available information. No new subjects would be added to the dose escalation stage after a maximum of 12 subjects enrolled in a single dose level.

Dose escalation decisions require a minimum of 2 DLT-evaluable subjects in dose levels 1 and 2, and a minimum of 3 DLT-evaluable subjects for all subsequent dose levels. For this study, the DLT observation period is defined as the first treatment cycle (Cycle 1, 28 days). Adverse events occurring after the DLT

observation period will also be reviewed and may be taken into consideration for ensuring dose escalation decisions. At least 6 subjects will be treated during dose escalation at what is ultimately declared the disease specific RP2D prior to commencing dose expansion at the same dose.

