### Part A and Part C

Subjects with R/R MM (Part A) will receive escalating doses of ABBV-467 as described above. Once a pharmacologically and/or clinically active and tolerable dose is identified based on review of totality of safety, efficacy, PK and PD data, this dose will be used to commence dose escalation in R/R AML (Part C), where provisional dose de-escalation will also be permitted.

In order to be considered DLT evaluable, a subject must either:

1. receive each of planned doses *and* at least 80% of the total planned dose of ABBV-467 for Cycle 1; or
2. experience a DLT after receipt of at least one dose of ABBV-467 during the DLT evaluation period.

Selection of doses used in the study, including the optimal biological dose (OBD) and RP2D, can be found in Section 4.2.

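### The protocol contradicts itself on the DLT period for AML (Part C), so it does not fix when a myelosuppressed subject may be counted in Table 1

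*Protocol*

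**What the plan says.** Three statements give 28 days with no AML exception:

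- Section 4.1, Dose Escalation Guidelines: "For this study, the DLT observation period is defined as the first treatment cycle (Cycle 1, 28 days".
- Section 6.3, opening: "Dose-limiting toxicity for dose escalation purposes will be determined on events that occur during the first 28-day cycle".
- Section 6.3, after the AML hematologic criteria: "The DLT evaluation period will be 28 days irrespective of dose frequency", followed by a parenthesis on the case that other schedules are studied.

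Two statements in the hematologic part of Section 6.3 go beyond 28 days:

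- The listed AML hematologic DLT is ANC below 500/mm³ and/or platelets below 25,000/mm³, with marrow blasts under 5%. It is read at Day 42 from first dose, at 14 days after ABBV-467 stops, or at both.
- The period is extended: "For AML subjects with evidence of myelosuppression at 28 days, the DLT period will be 42 days or 14 days after bone marrow biopsy" with blasts under 5%, taking the later of the two.

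Two statements govern evaluability:

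- Section 4.1, Part A and Part C: a subject is DLT-evaluable after every planned dose and "at least 80% of the total planned dose of ABBV-467 for Cycle 1", or after a DLT in the evaluation period. The extension is not mentioned.
- Section 6.3, last paragraph: the same dosing test is applied over the DLT evaluation period rather than over Cycle 1.

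Section 4.1 adds that events after the observation period are reviewed and may be taken into account. An escalation decision needs at least 2 DLT-evaluable subjects at dose levels 1 and 2, and at least 3 at later levels.

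**The concern.** Table 1 takes two inputs, the number of DLT-evaluable subjects and the number with a DLT. For an AML subject who is cytopenic at Day 28, the protocol gives two answers on whether the DLT question is closed. If it is treated as closed, the subject joins the denominator as DLT-free before the AML hematologic criterion can be read at Day 42. That error runs one way, toward escalation.

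The recommended Phase 2 dose in AML is a primary objective, and the toxicology summary (Supplementary Table S7) lists reduced marrow cellularity in both rat and dog. Late cytopenia is therefore an event that the design should count consistently. The DLT period defines the dose-finding endpoint, so it needs to be settled in the protocol itself.

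**Working it through.** **1. Reproduce the plan's boundaries.** Inputs from Section 4.1: target φ = 0.25, φ1 = 0.6 × 0.25 = 0.15, φ2 = 1.4 × 0.25 = 0.35.

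- Escalation: ln[(1−φ1)/(1−φ)] / ln[φ(1−φ1)/(φ1(1−φ))] = ln(0.85/0.75) / ln(0.2125/0.1125) = 0.1968.
- De-escalation: ln[(1−φ)/(1−φ2)] / ln[φ2(1−φ)/(φ(1−φ2))] = ln(0.75/0.65) / ln(0.2625/0.1625) = 0.2984.

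These match the stated 0.197 and 0.298. The escalate, stay and de-escalate rows of Table 1 reproduce for every n from 2 to 12.

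**2. What one event does.** Escalate at or below floor(0.1968n); de-escalate at or above ceil(0.2984n).

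| n | 0.1968n | Escalate if ≤ | 0.2984n | De-escalate if ≥ |
|---|---|---|---|---|
| 3 | 0.59 | 0 | 0.90 | 1 |
| 6 | 1.18 | 1 | 1.79 | 2 |

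There is no stay zone at n = 3 or n = 6 (nor at n = 2), so one uncounted DLT turns de-escalate into escalate. At n = 4, 5 and 7 to 12, one event moves the action by a single step at most: escalate to stay, or stay to de-escalate.

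**3. When the AML criterion can be read.**

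- The Day 42 reading comes 42 − 28 = 14 days after a 28-day window closes.
- Fourteen days after a last dose on Day 1, 8, 15 or 22 is Day 15, 22, 29 or 36. This reading falls inside 28 days only if dosing stops after Day 1 or Day 8.
- The Operations Manual (Section 3.16) places the marrow within 3 days of Cycle 1 Day 28, that is Day 25 to 31. Adding 14 gives Day 39 to 45. The later of that and Day 42 is Day 42 to 45.

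**4. One subject under each rule.** Take an AML subject who received all Cycle 1 doses and is cytopenic at Day 28 with marrow blasts under 5%.

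| Rule applied | Consequence |
|---|---|
| 28-day statements (4.1; 6.3) | Period closed at Day 28; no hematologic DLT can yet have been scored |
| AML extension (6.3) | Period open until Day 42 to 45 |
| Evaluability rule (4.1) | Met on Cycle 1 dosing; no time condition |
| Dosing test over the DLT period (6.3, last paragraph) | If the period runs to Day 42, Cycle 2 doses come into the test, yet Table 4 can interrupt dosing from Day 29 up to Day 42 for CRi or MLFS; read literally, the subject could become non-evaluable |

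These outcomes cannot all hold, and no sentence ranks the rules.

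**5. Illustration of size.** The split of early and late DLTs is not in the document. Assume that 25% to 50% of DLTs show only after Day 28 and are not counted. The probability that Table 1 indicates escalation is (1−p)³ at n = 3 and (1−p)⁶ + 6p(1−p)⁵ at n = 6, with p replaced by 0.75p or 0.5p when late events are missed.

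| True DLT rate | n = 3: all counted | n = 3: late missed | n = 6: all counted | n = 6: late missed |
|---|---|---|---|---|
| 0.25 | 0.422 | 0.536 to 0.670 | 0.534 | 0.686 to 0.833 |
| 0.35 | 0.275 | 0.401 to 0.562 | 0.319 | 0.505 to 0.717 |
| 0.45 | 0.166 | 0.291 to 0.465 | 0.164 | 0.343 to 0.594 |

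**The case against.** The strongest reply is that the specific rule governs the general one. The extension names AML and names the myelosuppressed subject, so on an ordinary reading that subject is still under DLT observation at Day 42. The last of the three 28-day sentences carries a parenthesis about other treatment schedules and is mainly about dosing frequency. Table 4's delay to Day 42 fits the extension. Escalation is not automatic either: Section 4.1 has decisions made on all available information and has later events reviewed. Section 6.3 also counts discontinuation for an adverse event of any grade, and a missed dose from toxicity not explained by the disease, as DLTs in AML too.

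Much of this stands. A reader might infer that the protocol has no means of counting the late AML event, or that Part C will escalate before it can be counted. The documents support neither. The extension is there, and early counting follows only if the 28-day statements override it or the evaluability rule is applied as written.

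A reader might also see a second bias in the note that begins "In any instance in which bone marrow response assessment is either undocumented, or consistent with", because it attributes such cytopenias to AML. That is a separate and weaker matter. The attribution is an explicit rule, and the Operations Manual (Section 3.16) requires marrow assessment, so an undocumented marrow should be a deviation and not a routine path. No replacement rule is called for here.

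What the reply does not remove is the conflict with Section 4.1 and the opening of Section 6.3, or the silence of the evaluability rule. Later events may be considered under Section 4.1, but they need not be counted.

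**Conclusion.** The point holds as an internal contradiction. The protocol does not fix which DLT period applies to a myelosuppressed AML subject, or when that subject may be counted as DLT-free. The exposure is 14 to 17 days per affected subject (Day 28 to Day 42 to 45), assuming that the marrow is done within its stated window. It concerns only subjects with marrow blasts under 5%. One uncounted event reverses the Table 1 action at n = 3 and n = 6, and shifts it by at most one step at n = 4, 5 and 7 to 12.

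The probabilities in the illustration rest on an assumed share of late DLTs and on the less favorable reading. They show direction and possible size and do not predict conduct. The BOIN boundaries and Table 1 are correct as printed. The sample size is not affected.

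**What to change.** Reconcile Section 4.1 (Dose Escalation Guidelines; Part A and Part C) with Section 6.3 before Part C opens:

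- Cross-refer to the AML extension where Section 4.1 defines the observation period and in the opening of Section 6.3.
- Except the extension from the later 28-day sentence in Section 6.3, so that this sentence speaks only to dosing frequency.
- State that a Part C subject whose DLT period is extended is not counted in Table 1 as DLT-evaluable without a DLT until that period closes.
- State in both sections that the dosing-completeness test refers to Cycle 1 doses and not to the extended period.

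This uses the extension already in the protocol and adds no new threshold or time point. The cost is wording, plus a wait of about two weeks or slightly more for some Part C decisions.
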